### Intervention

Northwestern Medicine’s® (NM) Comprehensive Transplant Center launched the Hispanic Kidney Transplant Program (HKTP) in December 2006 to address the needs of the growing underserved Hispanic population in Chicago. The NM® HKTP is culturally targeted by employing bicultural and bilingual staff, using Spanish in patient/family-provider communications and written materials, and addressing commonly shared Hispanic cultural values, beliefs, misconceptions, and information needs of Hispanic ESRD patients and potential living donors [67], as previously described [20, 68]. HKTP’s culturally targeted components correspond closely with the National Quality Forum’s (NQF) Framework for Standardizing Measurement and Reporting of High-Quality, Culturally Competent Care (Table 1) [20, 69].

**Table 1 Tab1:** Implementation fidelity for each intervention component, and moderating factors affecting fidelity

Intervention component ID #	Intervention component description	NQF dimensions	Data source
*For patients at the dialysis center:*			
1	At the dialysis center, the bilingual (bicultural) outreach staff hold lobby days to introduce, hand out an information folder in Spanish about the HKTP, and invite Hispanic patients to attend the HKTP. Staff provide patient contact information to clinic schedulers to set up a clinic visit for each patient.	Workforce diversity and training; Data collection, public accountability, and quality improvement; Community outreach	-Observations -Checklist -Survey-Metrics
2	Transplant center telephone bilingual* schedulers offer (follow the script) the HKTP clinic as an option to all Hispanic patients calling to schedule transplant evaluation, regardless of the patient’s spoken language. Schedulers encourage patients to bring their family members to the HKTP visit.	Integration into management systems and operations; Workforce diversity and training	-Audio-Recordings
3	Establish a Spanish speaking telephone line at the transplant center.	Integration into management systems and operations	-Survey-Metrics -Learning Collaborative
4	The transplant center’s phone line offers (live) Spanish-speaking schedulers when patients call.	Integration into management systems and operations	-Survey-Metrics
*For patients and family who visit the HKTP:*			
5	Bicultural Transplant surgeon delivers the 2 back-to-back HKTP education sessions that provide same care as the English program as well as address cultural concerns about transplantation in Spanish.	Patient-provider communication; Workforce diversity and training; Integration into management systems and operations	-Observation-Site Visit -Observation-Research Staff -Survey-Metrics -Audio-Recordings
6	Education sessions address Hispanic cultural and religious concerns & myths.	Patient-provider communication	-Audio-Recordings
7	Education sessions include family members in both sessions.	Patient-provider communication	-Observation-Site Visit -Observation-Staff -Survey-Metrics
8	Bicultural transplant surgeon or bilingual transplant nephrologist holds a ‘wrap up’ clinical visit with each patient and asks about available potential living donors.	Patient-provider communication	-Survey-Metrics -Observation-site Visit
9	HKTP bilingual clinical staff and/or outreach staff contact patients who have not completed evaluation within 10–12 weeks.	Care delivery and supporting mechanisms	-Medical chart review
10	HKTP Director calls patients and referring MD if patients have not completed pre-transplant evaluation by 8–10 and 12 weeks.	Leadership; Care delivery and supporting mechanisms; Community outreach	-Medical chart review
11	Availability of interpreters or interpreter services.	Workforce diversity and training	-Phone calls
12	Data collection on patients in a transplant database for quality assurance and identifying areas for improvement.	Data collection, public accountability, and quality improvement	-Phone calls
*For the local nephrology community:*			
13	Letters are mailed to nephrologists introducing the HKTP to increase patient referral.	Community engagement	-Medical chart review
14	Transplant center holds in-service presentations to local social worker and nephrology organizations to increase awareness of the HKTP to increase patient referral.	Community engagement	-Survey-Metrics -Phone calls
*For the public:*			
15	Transplant center engages in marketing events (e.g., interviews in news and social media) about the HKTP directed to the Hispanic community in Spanish (TV, radio, newspaper).	Patient-provider communication; Community engagement	-Survey-Metrics -Phone calls
16	Transplant center website hosts information about the HKTP in Spanish.	Patient-provider communication	-Survey-Metrics -Phone calls

#### Community engagement

Outreach to the community is vital for increasing the number of patients referred to the HKTP. Bilingual/bicultural outreach staff (e.g., social workers) will hold 3 to 4 “lobby days” at dialysis centers per month. This will entail setting up a booth in the lobby to educate dialysis patients in Spanish about transplantation, address questions, and invite patients to come to the HKTP for transplant evaluation. The outreach staff will give patients materials describing the HKTP written in Spanish and English. When patients express interest in transplantation, the outreach staff will obtain patients’ contact information and hand out their business card. Upon returning to the transplant center, the outreach staff will enter a note in the transplant scheduling database and/or call patients back to confirm interest. The note in the database will trigger an email to the scheduler to call the patient to schedule an appointment.

#### Care delivery and supporting mechanisms

Transplant centers will mail letters to all referring nephrology and primary care practice groups to inform them about the HKTP and increase referrals of Hispanic patients. Transplant centers, as part of routine care, notify referring nephrologists by phone or letter when their patients initiate evaluation or receive a transplant; the intervention will incorporate informing nephrologists about the HKTP into such communications. HKTP facilitators and staff will also sponsor in-service education sessions or conferences to educate the local nephrology and social worker communities about the HKTP program. Additionally, transplant center staff and faculty (site PIs) will contact potential recipients, by telephone and/or mailed letter, who have not completed their transplant evaluation to remind them to complete the process.

#### Integration into management systems and operations

When referred Hispanic patients call the transplant center to set up their initial transplant evaluation visit, the schedulers who set up appointments will follow a script. The script will briefly describe the education sessions in the HKTP and the routine English transplant programs, explaining that the HKTP delivers the same medical care as the English program, but is provided in Spanish by bilingual and bicultural transplant clinicians, and addresses Hispanic cultural concerns. At the end of the script, the schedulers will ask Hispanic patients whether they prefer the HKTP or the English clinic. If patients prefer the HKTP clinic, then schedulers will encourage patients to bring friends and family members, including family elders, with them to the HKTP clinic.

#### Patient-provider communication

The Hispanic, bilingual physician (Directors of the HKTP at each site) will deliver HKTP clinics twice per month, each of which entails two sequential educational sessions in a group setting in Spanish, at the beginning of kidney transplant and live donor evaluation. Session 1 will be delivered to potential recipients, family, and potential living donors, and will discuss kidney transplantation, deceased and living donation, and will address cultural and religious concerns commonly held by Hispanics. Session 2 will be delivered to friends, family members, and potential living donors and will cover more specific information about living donation, while potential recipients receive initial clinical evaluation.

Bilingual and bicultural Hispanic transplant clinical staff and faculty will clinically evaluate patients after the education sessions. After Session 1, staff will obtain patients’ history and physical information. After Session 2, the physician Director will hold a wrap-up visit one-on-one with patients and their family members to ask the patient for their verbal report of available living donors who have expressed an interest in donation, and address further questions and misconceptions about donation and transplantation. Potential donors will be evaluated on a separate day to avoid the potential for coercion.

#### Marketing

The intervention will entail marketing to the general public to increase awareness of the HKTP. The transplant centers will revise their current websites by including information about the HKTP in Spanish and English. The site PIs at both transplant centers, who deliver the HKTP education and thus serve as the face of the HKTP, will engage in news media interviews and public service announcements targeting the Hispanic community (e.g., via Spanish-language television, radio, newspaper) about Hispanic disparities in transplantation and the availability of the HKTP to address this problem.

#### Data collection, public accountability, and quality improvement

Both study sites will modify their current transplant databases to account for every Hispanic potential recipient and potential living donor to facilitate patient management and data analysis of patients’ referrals to the HKTP, and their evaluation status until wait-listing and transplant. Databases will also be updated, as needed, to track Hispanic nationality.

### Study design overview

A prospective effectiveness-implementation hybrid design [70] involving pre-post intervention evaluation with matched controls will be used to implement and evaluate the HKTP. Due to design, matched control sites were pre-specified, and were matched with intervention sites based on city population size, Hispanic proportion of the city population, and kidney transplant and LDKT volumes. Although an ideal study design would be a randomized controlled trial that randomizes patients within each center, it is laden by contamination effects. Randomizing at the center level would require a large number of centers to serve as intervention sites and controls, which is costly. To assess other secular trends, data from matched control centers that do not implement the HKTP will be compared. Control sites were selected in different cities than intervention sites to avoid contamination from local implementation efforts. The first year will focus on implementing the HKTP at BUMC and MC over a 12-month period (Aim 1). Remaining years will focus on evaluating the HKTP on Hispanic LDKTs and on program fidelity in years 2–4½ (Aims 2 and 3).

The hypotheses are that the HKTP will lead to a(n):H_1_ Increase in the ratio of Hispanic to non-Hispanic white LDKTs and in the number of Hispanic LDKTsH_2_ Increase in the number of Hispanic ESRD patients added to the waiting listH_3_ Increase in the number of Hispanic potential donors per potential recipientH_4_ Greater satisfaction of Hispanic ESRD patients with culturally competent care

AIM 1: To implement the HKTP at Two Transplant Centers.

The NU team will first provide BUMC and MC with a preliminary set of protocols comprising the HKTP manual of operations, scripts for clinical coordinator and outreach staff to use, and educational materials describing the structure and content of the education sessions and transcriptions. To train the staff and providers at BUMC and MC, a video-based curriculum will be provided that explains the outreach staff’s communications with dialysis patients, and demonstrates NM’s HKTP Director’s education sessions. NM’s HKTP education session PowerPoint slides will also be provided for sites to use. The set of protocols will help BUMC and MC to determine how to modify their organizations to accommodate the HKTP. Publications that provide evidence to support the HKTP’s increase in Hispanic LDKTs will be provided to foster site ‘buy in’ to implement the HKTP [20, 68].

*Site Visit* [name] and [name] (co-PIs) will conduct a site visit in year 1 to perform the needs assessment to identify transplant provider-, administrator-, and center-related barriers and facilitators to the implementation and sustainability of the HKTP, in order to refine and deliver the final set of protocols, scripts, and educational materials. During the needs assessment, [name] will use ethnographic methods [71] to interview, observe, and survey BUMC’s and MC’s transplant physician (and/or site-PI), staff (outreach staff), and administrators involved in HKTP implementation (total n = ~ 5 per site).

*In-Depth, Qualitative Interviews* will assess the current workflow and where changes could be made within the workflow to comply with the HKTP protocol. Interviews will be audio-recorded and last 30–45 min.

*The “Learning Collaborative”* [72, 73] method will be used to help BUMC and MC staff design center-customized approaches and solutions to barriers to implementing the HKTP. This short, rapid approach to healthcare quality improvement is often used by organizations and providers to work collaboratively by sharing their experiences and best practices to accelerate learning [74, 75]. This approach can increase critical thinking and leadership skills more than individual learning [76, 77], and enhance the observability and trialability of the HKTP -- characteristics identified as important in Revised PARIHS evidence framework. Staff from BUMC and MC will visit the NU research team in month 7 for a 2-day “learn together” program [78] to discuss their challenges and strategize on overcoming problems with implementing the HKTP at their institutions. During the in-person meeting, BUMC and MC staff will shadow and role-play with NU staff to practice communicating with patients and responding to patients’ questions. Additionally, the Learning Collaborative will entail routine telephone calls between program staff to benchmark against each other and NM’s HKTP to identify best practices and learn from one another. The NU research team will continuously help troubleshoot ways that BUMC and MC can increase readiness and adapt the HKTP into their programs, using NQF guidelines and the cultural competence analytic framework [65, 69]. Through collaborative learning, BUMC and MC staff will obtain the social support necessary to overcome isolation of going through the implementation process alone.

Based on data analysis of the needs assessment, a subsequent, final set of protocols, scripts, and materials that integrate modifications to the HKTP that adapt the HKTP to each intervention site will be created and provided. Remediation plans will be used to assist intervention sites in implementing the protocols, as needed, if deficiencies are detected by the research staff or observed during site visits.

Formative evaluation procedures will be used to optimize intervention implementation (fidelity) [79], and enhance the HKTP, as the NIDDK program announcement requires [80]. Specifically, the delivery of *dosage* and *coverage* of required programmatic elements will be evaluated to determine whether all intervention components were implemented as planned, and to identify which parts of the HKTP worked best. Monitoring will occur weekly during implementation (months 0–8), twice per month for adjustment (months 9–12), and monthly for process checks (months 13–54). Given that people’s actions typically differ from what they say they do [71], we will use mixed methods [81] to assess actual behaviors.

AIM 2: To evaluate how factors from the CFIR and the Revised PARIHS frameworks and emergent factors unique to the implementation of culturally competent care affect fidelity.

### Mixed methods research

We will use a mixed-methods approach using qualitative and quantitative research methods to obtain broader insights than either method could provide alone, to enable further clarification of findings generated by a single method, and to enhance the validity of findings [81–83]. Qualitative methods include: site visits, semi-structured interviews, observations, and routine telephone discussions. Quantitative methods will include surveys and checklist evaluations.

*Routine telephone calls* will be conducted by [name] with a NU research staff member, and each site’s research staff member on a weekly basis for the first 18 months, and on a biweekly basis thereafter. During the phone calls, [name] will informally ask about the progress of the IRB, the delivery of HKTP clinics, number of patients, barriers to implementation, problems with delivery, and brainstorm solutions. The phone calls will last 30–60 min. [name] will also hold ad hoc telephone meetings or email correspondences with each physician (site PI) for updates and progress made on the implementation and intervention delivery. Field notes will be taken during all correspondences.

*Learning collaborative telephone calls* will be conducted quarterly by [name] with a NU research staff member and appropriate front-line staff from the two transplant centers. These phone calls will last approximately 60 min. During these phone calls, comparative intermediate outcomes will be benchmarked from the two transplant centers, and staff will share best practices they have developed for overcoming obstacles and achieving better results. These interviews will be recorded and transcribed.

*Routine site visits* will be conducted by [name] and [name] each year to assess progress, extent of tailoring, strengths, and obstacles related to the HKTP implementation.

*Semi-structured Interviews* will assess organizational readiness to change, each site’s disposition to using evidence for adapting the HKTP into practice, organizational culture, and barriers and facilitators to implementing each respondent’s respective HKTP component, using Stetler and colleagues’ Guide for each revised PARIHS construct [58]. Interviews will be conducted in person (during site visits) or by telephone with the clinical team (e.g., faculty, administrators, staff) and research staff, will last 30–60 min, and will be audio-recorded and transcribed.

*Organization surveys* will assess BUMC’s and MC’s readiness to change, facilitation capacity, and disposition to accepting evidence about the HKTP’s effectiveness to implement change, using the validated, Organizational Readiness to Change (ORCA) instrument (Cronbach’s alpha = 0.74–0.95) [84]. ORCA surveys will be self-administered on paper by the clinical team and research staff before the first site visit.

*Online surveys* will be completed by the research staff (via Research Electronic Data Capture (REDCap)) that assess metrics about key HKTP components on a monthly, quarterly, or biannual basis based on observation or information provided by the outreach staff. For example, the frequency of outreach visits to dialysis centers per month, the number of Hispanic patients met per visit, the number of patients who express an interest in coming to the HKTP for evaluation per visit, the number of these patients who share their contact information with the outreach staff, the number of these patients who schedule an appointment, the number of patients who show up to each HKTP education session, the number who complete the evaluation process and get waitlisted for transplantation, and the number who get a transplant by type of transplant. Additionally, the research staff member will track through online surveys the number of HKTP education sessions per month, and marketing efforts. Finally, research staff will assess whether their hospital’s patient advocacy department has received any concerns from patients or families with the HKTP program on a quarterly basis through a single-item survey.

*Observations* will be conducted in two ways. (1) During the site visits, [name] will conduct observations of the dialysis outreach, telephone communications, and educational sessions in practice to see how they occur and to learn about the organizational culture. (2) During routine intervals, research staff will shadow outreach staff as they perform outreach at dialysis centers, and observe faculty delivering the education sessions monthly (months 13–54) to identify potential discrepancies from the HKTP protocols and scripts to amend.

*Checklists* will be completed by research staff while observing the outreach staff and the HKTP education sessions to track adherence to HKTP protocols and scripts. Completed checklists, metrics, surveys, and audio-recordings will be reviewed by the NU research team to identify potential problems and solutions to improving the HKTP on a quarterly basis.

*Audio-Recordings* will be made of two HKTP components: (1) telephone conversations between schedulers and patients calling to schedule an appointment, one day per month. Patients (*N* = ~ 75) will first be informed that “This call may be monitored for quality control” and asked for their verbal consent to be audio-recorded. (2) HKTP educational sessions led by the site PI delivered to ESRD patients and their family, once per month. All recordings will be electronically sent to the NU research team. Inter-rater reliability will be assessed by the intervention site’s research staff and NU’s research staff [85] to identify gaps or errors in the delivery of telephone communication or educational content, and determine whether retraining is needed.

### Qualitative analysis

Qualitative data and field notes from the needs assessment and follow-up interviews will be analyzed for themes and patterns emergent from the data [86, 87], using the constant comparative [88], deductive and inductive coding methods [89]. [name] will develop an initial deductive code list a priori, based on the PARIHS and CFIR framework domains, and [name] will train the research staff on how to apply it to interview transcripts and field notes. Analytic retreats will then be held with research staff (led by [name]) to inductively develop additional codes within each domain, in an iterative process. The retreats will entail comparing codes, resolving discrepancies in code meaning and use through discussion, and revising the codebook. Codes will be revised to account for new observations, continuing until saturation is reached [90]. Analytic insights and decisions made during the retreats will be captured in minutes taken by the research staff. Qualitative analysis software (MaxQDA) will be used to support analysis, and [name] will meet with the research staff to monitor coding quality and timeliness.

We will use Stirman, Miller, Toder and Calloway’s framework for coding modifications [91] and classification system of reasons for adaptations to evidence-based interventions [92]. This coding scheme will allow us to assess the types of content and contextual modification to the HKTP. Additionally, through qualitative analysis, we will determine the reasons for these modifications. Finally, we will determine the impact of these modifications on the outcomes of the HKTP from outreach to transplant. We will compare similarities and differences in modifications across study sites.

### Statistical analysis

Descriptive statistics of metrics will be used to assess extent of fidelity to implementation. Bivariate analyses involving t-test comparisons of ORCA data will be conducted to compare level of readiness between study sites.

AIM 3. To conduct a pre-post HKTP intervention evaluation with matched controls to evaluate the effect of the HKTP, and the influence of innovation adaptations, on intermediate and final outcomes.

### Outcome measures

We will assess the reduction in disparities between self-identified Hispanics and non-Hispanic whites in LDKT rates for adult-to-adult living kidney donation. The effectiveness of the HKTP will be assessed by comparing the outcomes before introducing the HKTP and after the HKTP has been fully implemented. Measures will be collected at intervention and control sites in pre and post periods. For the final outcome measures, de-identified, aggregate center-level data will be collected from the Organ Procurement and Transplant Network/United Network for Organ Sharing (OPTN/UNOS) as publically reported data (Table 2). Data from sites’ medical record review will also be collected. Intermediate outcome measures about each Hispanic and non-Hispanic white potential recipient and potential donor will be collected monthly by research directly from intervention and control sites by medical record review to assess the pathways by which the HKTP potentially increases rates of Hispanic LDKT. We expect that the pre-post change will demonstrate a higher number of potential donors who initiate evaluation and complete more steps in the donor evaluation process.

**Table 2 Tab2:** Final and Intermediate outcome measures: transplant center-reported

Construct	Measure description
Final outcomes	
Ratio of Hispanics to Non-Hispanic Whites Receiving LDKTs	This ratio takes into account growth in transplant center volume while also providing a comparison to non-Hispanic whites, necessary for assessing disparities in LDKT [102]. The ratio provides an index of whether the Hispanic LDKT increase has grown over and above the increase observed at a center overall. By using this ratio, factors related to the center’s infrastructure and capacity to perform additional LDKTs that affect both Hispanics and non-Hispanic whites equally are accounted for. Institutional commitments to LDKT that are associated with higher rates of LDKT, can influence willingness to donate or preferences for LDKT, and affect both populations equally (e.g., paired donation, and desensitization efforts), are accounted for.
Number of Hispanic LDKTs	Change in number of Hispanic LDKTs compared to change in number of non-Hispanic white LDKTs will provide evidence that the increase is not at the expense of white patients.
Number of Hispanic Patients Added to the Waiting list:	An increase in this number indicates success in overcoming barriers in gaining access (referral) to transplantation and completing the evaluation [103].
Number of Hispanic Potential Donors per Potential Recipient	An increase in this proportion reflects success in encouraging more potential living donors to undergo donor evaluation.
Intermediate Outcomes	
# Patients referred by outreach	The aggregate number of patients who were referred by outreach staff. Referral can be made by self, staff at dialysis centers, nephrologists, primary physicians, or transplant outreach staff.
# Patients scheduled/attending the education session	The aggregate number of patients who were scheduled and attended the HKTP education sessions.
# Patients who completed evaluation	The aggregate number of patients who completed the transplant evaluation process.
# Patients waitlisted	The number of additions to the transplant center’s own waiting list will serve as a proxy for access to the waiting list.
# Days on waiting list, dialysis time	The number of days patients have waited on the waiting list to date.
# Pre-emptive transplants	The number of patients who received a living donor transplant prior to going on dialysis.
# Potential donors at each phase of evaluation	The aggregate number of potential living donors who have completed each phase of the donor evaluation process.
# Days for donor to complete each phase of evaluation	The number of days from start to finish of each phase of living donor evaluation from initiation to clearance for donation to donation.
Potential donor disposition	The donor’s evaluation status as: initiated, completed, ruled out, withdrew, alternate donor found.
Contextual Outcomes	
Patient and potential donor socioeconomic status	Age, gender, race/ethnicity, insurance.
Organ Procurement Organization and transplant center factors	ESRD incidence, and transplant center volume.

Hispanic patients’ and family members’ satisfaction with culturally competent care will be evaluated before and after implementing the HKTP by using the validated, closed-ended, DHHS AHRQ Consumer Assessment of Healthcare Providers and Systems (CAHPs) Cultural Competence Item Set (34 items) [93, 94] and Patient Centered Medical Home subset (8 items) [88, 89]. Topics covered include: patient-provider communication, shared decision making, preferences for shared decision making, experiences leading to trust or distrust, experiences of discrimination, and linguistic competency. Surveys will be self-administered on paper in the clinic waiting room after completing clinic visits that day. A total of *n* = 70 patients/donors will be surveyed at each site in year 1 (pre-HKTP) and year 5 (post-HKTP) [93], in English or Spanish [95].

Contextual measures will also be collected from all sites to control for confounders through routine phone call communications with study sites. News items and policy changes will also be scanned for secular effects on data collection or HKTP outcomes. For example, the research team will take note of international, national, regional, and hospital news items pertaining to health disparities, Hispanics, and/or organ transplantation/donation.

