### Statistical analysis plan

SAS version 9.4 (Carey, NC) will be used for analyses. Testing of each hypothesis will be performed separately for each study site. For Hypotheses 1 and 2, quarterly UNOS outcome data (6 years pre- and 3.5 years post-HKTP) will be used to model ethnic and racial differences in transplants, to account for external events that could alter LDKT rates, and to analyze the sustainability of the HKTP intervention. Hypotheses 3 and 4 will be evaluated with monthly data. Associations between final outcome and intermediate outcome measures, and individual patient and donor level variables will be evaluated. Matched intervention and control sites will be compared.

To test hypothesis 1, we will use OPTN/UNOS data, to construct the ratio of the number of Hispanics receiving LDKTs to the number of non-Hispanic whites receiving LDKTs for each center from 6 years prior to 3.5 years after implementation of the HKTP. An interrupted time series (ITS) design with segmented regression analysis will be used to assess the HKTP. Ratio data will be collected across 24 quarterly time points pre-intervention (reference point), and 14 time periods post-intervention for a total of 38 time-series data points for each center.

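### H3 is stated as a Hispanic-only rise in donors per recipient; without a within-centre non-Hispanic white contrast, the matched control cannot separate an HKTP effect from a donor-recruitment gain confined to the intervention centre

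*Protocol article*

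**What the plan says.** The Study design overview states H3 as an increase in the number of Hispanic potential donors per potential recipient. Table 2 (Outcome measures) lists this measure among the final outcomes and explains it with the sentence "An increase in this proportion reflects success in encouraging more potential living donors to undergo donor evaluation". Neither place names a comparison group.

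Both H1 measures in the same table have one. Of the Hispanic to non-Hispanic white LDKT ratio, the table says "The ratio provides an index of whether the Hispanic LDKT increase has grown over and above the increase observed at a center overall", and that capacity and infrastructure factors "that affect both Hispanics and non-Hispanic whites equally are accounted for". The entry for the number of Hispanic LDKTs refers to "Change in number of Hispanic LDKTs compared to change in number of non-Hispanic white LDKTs".

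On data, Outcome measures says "Intermediate outcome measures about each Hispanic and non-Hispanic white potential recipient and potential donor will be collected monthly", at intervention and control sites.

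On analysis, the Statistical analysis plan section says that quarterly registry data for H1 and H2 "will be used to model ethnic and racial differences in transplants". For H3 it says only "Hypotheses 3 and 4 will be evaluated with monthly data". It adds "Testing of each hypothesis will be performed separately for each study site" and that matched intervention and control sites will be compared, without limiting that comparison to particular hypotheses.

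**The concern.** H3 is the donor step through which the HKTP is expected to raise Hispanic LDKTs. The measure is already per recipient, so growth in centre volume is not the difficulty. The difficulty is a change in donors per recipient that reaches every patient at the intervention centre, such as a stronger living-donor effort for all.

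The article sees this threat under H1. Table 2 names institutional commitments to LDKT that can alter willingness to donate and act on both ethnic groups alike, and gives the white comparison as the way to account for them. Willingness to donate bears even more directly on donors per recipient than on completed transplants, yet H3 has no such comparison.

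At stake is what a positive H3 would mean. Hispanic and white donors per recipient could rise together, leaving the gap as it was, and H3 as worded would still be met. The donor step would then appear to support an HKTP pathway that had not operated.

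**Working it through.** **Plan's own figure.** The article gives no sample size, effect size or power for H3, so there is nothing to reproduce. Everything below is an illustration on assumed values.

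**1. What each comparison removes.** Let s be a trend shared by all sites, g a gain across the whole intervention centre, and h the HKTP effect. The post/pre ratio of donors per recipient is s·g·h for Hispanics at the intervention site, s·g for whites there, and s for both groups at the control site.

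- Hispanic pre-post: s·g·h
- Hispanic, intervention against control: s·g·h / s = g·h
- Hispanic against white within the intervention site: s·g·h / (s·g) = h
- The last contrast, set against the same contrast at the control: h / 1 = h

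Take s = 1.10, g = 1.3 and h = 1.0 (no HKTP effect). The four results are 1.43, 1.30, 1.00 and 1.00. The control site takes out s and leaves all of g. With h = 1.2, the last two return 1.20 whatever g is.

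**2. How often this would give a significant H3.** Assumptions: Poisson donor counts; 300 Hispanic potential recipients per period at the intervention site and 300 at the control; 1.0 donor per recipient before launch; no HKTP effect; a rise by factor f at the intervention centre only; control unchanged. Work on the log rate ratio:

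SE = √(1/300 + 1/(300f) + 2/300), and P(significant in favour) = P(Z > 1.96 − ln f / SE).

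| f | ln f | SE | ln f / SE | P |
|---|---|---|---|---|
| 1.1 | 0.095 | 0.114 | 0.83 | 13% |
| 1.2 | 0.182 | 0.113 | 1.61 | 36% |
| 1.3 | 0.262 | 0.112 | 2.34 | 65% |

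The nominal one-directional rate is 2.5%. With 200 Hispanic recipients per period at each site, the figures are 10%, 26% and 48%. If the rise also occurs at the control, the rate returns to 2.5%.

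**3. Price of the white contrast.** Add 450 white recipients per period (assumed) at the same rate, with f = 1.2:

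- Hispanic-only pre-post: SE = √(1/300 + 1/360) = 0.078
- Hispanic against white within site: SE = √(1/300 + 1/360 + 1/450 + 1/540) = 0.101
- Ratio: about 1.29, so the SE is about 29% larger

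Setting the contrast against an unchanged control with the same 300 and 450 recipients gives SE = √(0.101² + 2/300 + 2/450) = 0.146, against 0.113 for the Hispanic-only control comparison. The ratio is again about 1.29. Under a gain that affects both groups equally, the expected value of the white contrast is zero on the log scale, so its error rate stays at 2.5%.

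**The case against.** A reader might infer that the plan counts any rise in the Hispanic figure as success and credits it to the HKTP. The document does not support that. The Table 2 sentence describes what the measure reflects and is not a decision rule. Aim 3 is a pre-post evaluation with matched controls, measures are collected at control sites, and the site comparison is not restricted to H1 and H2. An uncontrolled pre-post test under the assumptions above would be significant in about 22%, 64% or 93% of trials, but that is not the stated design, so those figures should not be used.

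Several further points have force.

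- Publicity that also reaches the control city is handled by the control comparison, and the team will scan news and record contextual measures. However, the centre-level factors listed in Table 2 are ESRD incidence and transplant volume, and neither measures living-donor recruitment effort.
- The article is condensed, and a fuller plan may specify the H3 model. Nothing says the white data are barred from it. This limits the point to the hypothesis and its interpretation, which are stated here and are Hispanic-only.
- The Discussion notes that spill-over to white patients would favour the null and offers a Hispanic-only count as protection. This stands, and it argues against replacing the Hispanic-only ratio with the contrast.
- The disparity question is carried mainly by H1, and the document reports no centre-wide donor push at either intervention site. The threat is therefore a possibility, not something known to have occurred.

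**Conclusion.** The point holds in a limited form. As stated, H3 has no within-centre white contrast, although the article's own reasoning under H1 calls for one and the data are to be collected. There is one matched control per intervention site, in a different city, with testing done site by site. That comparison removes shared trends but passes on in full any gain confined to the intervention centre.

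Under the assumed counts, a gain of 10% to 30% of that kind would be significant in favour of the HKTP in roughly 13% to 65% of trials, or 10% to 48% with 200 recipients per period. The direction of the bias does not depend on the counts. Its size does, and the counts, the baseline rate and the gains are all assumptions. This is a cheap improvement to how H3 is tested and read, not a flaw that undermines the study.

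**What to change.** Keep the Hispanic-only ratio and its matched-control comparison. Add to H3 a test of the pre-to-post change in donors per recipient among Hispanics relative to the same change among non-Hispanic whites at the same centre, set beside the same contrast at the matched control. Reword the Table 2 entry so that a Hispanic-only rise is attributed to the HKTP only in light of that contrast.

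The cost is some wording and one further analysis of monthly records already planned at all sites. There are two downsides. The contrast is less precise than the Hispanic-only pre-post comparison (SE about 29% larger under the assumed counts). Spill-over to white patients would also shrink it. For both reasons it should be added beside the Hispanic-only measure and should not replace it. If the two disagree, report both and discuss spill-over and a centre-wide gain as competing explanations.
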